### Economic analysis

Readily available unit costs [40] will be attached to all items of resource use and a mean cost per participant estimated. QALYs will be calculated using EQ-5D with incremental cost and incremental benefits (effectiveness and utility) reported within an incremental cost-effectiveness ration (ICER). In addition, in line with the primary outcome measure, the economic evaluation will estimate the incremental cost-per-fall averted. Carer QOL will be calculated and reported separately. The evaluation will adhere to guidelines for good economic evaluation practice [41,42]. Analyses of costs and effects will be undertaken in Stata adhering to good practice for economic evaluations alongside clinical trials [43,44]. Missing cost and QOL data will be explored by employing multiple imputation methods [45,46] using alternative configurations of baseline covariates. The economic evaluation will be reported according to recent guidance [47].

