**Methods/Design:**

A UK multi-centre, community-based, single blind, randomised controlled trial with twelve month follow-up, and nested economic evaluation and qualitative studies will be undertaken. Six hundred PwP who live in their own home, have had one or more falls in the previous year and an MMSE score of ≥24 will be recruited. Those living in care homes and those needing assistance from another person to walk indoors will not be eligible.

The intervention is a physiotherapist delivered, individually tailored and progressive, home-based programme (PDSAFE) comprising task orientated movement strategy training, functional lower limb strengthening and balance training, of six months duration. Unsupervised daily home exercises and strategies will be practised and supported using technology. Control participants will receive usual care.

Data collection will include falls, cognitive state, balance and mobility, fear of falling, freezing of gait, mood, quality of life, carer quality of life and resource use. Data will be collected at baseline, three, six and twelve months. Longitudinal semi-structured interviews will be undertaken with forty participants to explore the expectations and experiences of participants.

The primary outcome is risk of repeat falling at six months post-randomisation.

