### Follow-up assessment

Follow up data (Table 1) will be collected at three, six and twelve months post-randomisation during a face-to-face visit to the participants’ home by an assessor blinded to group allocation. Serious adverse events (SAE) have been defined as hospitalisation as a result of a fall directly linked to the treatment with a therapist or whilst doing it on their own. Previous experience within the team suggests that participants may inadvertently unblind assessors. We aim to minimise this through explicit reminders prior to assessment visits. We will also ask assessors to record their estimate of which study arm they believe participants have been allocated to, and their confidence in that belief at the end of the trial. This will enable us to examine the extent of unblinding. Assessments will last approximately 90 minutes and, where possible, all assessments for an individual will be arranged for a similar time of day at mid-medication cycle when movement is optimal.

Fall data will be collected using monthly, prospective, self-report diaries for twelve months following randomisation and will include falls, near falls and injuries [34]. In addition to the diary, participants will be provided forms to completed details of any falls such as location and subsequent treatment [35]. The diaries will be delivered by the assessor at assessment visits and returned each month in a pre-paid envelope and with telephone reminders when not received within three weeks.

The implementation of the intervention protocol in terms of quality and dose will be monitored [36]. Joint patient sessions will be undertaken with the lead physiotherapist to assess intervention fidelity. Participant adherence to the unsupervised programme will be established by them completing a daily tick sheet of the exercises they have completed.

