For the economic evaluation, resource use (health and social care) and carer data will be collected using a tick box resource sheet aided by a resource use diary. Additional resource use will be collected within the fall dairies. Information on hospital admissions, length of stay, ambulance call outs, A&E attendances, GP and specialist appointments, physiotherapy, occupational therapy and admission to a care home will be identified and measured. Costs of implementing PDSAFE include training, time to deliver the intervention (face-to-face and telephone), travel, equipment and DVD production will also be identified and measured. Participant quality of life (QOL) data will be collected using the EuroQOL EQ-5D instrument [37] during assessment visits to enable the measurement of Quality Adjusted Life Years (QALYs). To capture any potential spillover QOL impacts carer data will collected using the Carer Experience Scale (CES) [38] and the Caregiver Strain Index (CSI) [39].

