### Statistical analysis

The main analysis will be based on intention to treat in that participants will be analysed according to the group to which they were allocated irrespective of the extent of intervention received. The primary outcome, risk of repeat falling over the 6 month period after randomisation, will be compared between intervention and control groups using a logistic regression model including falling during the pre-randomisation monitoring period, Hoehn and Yahr score, and centre as covariates, with the definition of the falling covariate decided at blind review of the data prior to analysis.

Repeat falling during 6–12 months and other binary secondary outcomes will be examined using logistic regression models similar to that for the primary outcome. The rates of falling over 0–6 months and over 6–12 months will be examined in negative binomial models including baseline rate of falling over the 3 month pre-randomisation falls collection period, Hoehn and Yahr score, and centre as covariates, fitted using either the *nbreg* or *xtpoisson* regression commands in Stata (Statacorp, TX, USA). In the negative binomial model, the effect of the intervention is summarised as a falls incidence rate ratio (IRR) (intervention/control) with ratios below 1.00 indicative of lower rates in the intervention group. All participants in the main trial will have been asked to complete the baseline three months falls collection, and the length of follow-up time over which falls events are collected between 0–6 months and 6–12 months post randomisation will be included as exposure times in the regression. Rates of falling in each of the three month periods between the pre-randomisation period and 12 months in the intervention and control groups will be displayed graphically. Other secondary outcomes will be examined in mixed normal models for repeated measurements at 3, 6 and 12 months controlling for centre, Hoehn and Yahr score, and baseline value, including participants with incomplete follow-up information in the analysis. No formal interim analyses are planned.

Sensitivity analyses will be conducted to examine the impact of missing data due to causes other than death, using worst-case and other single imputation on conclusions. Since only participants successfully completing the initial three months falls diary collection period will be entered into the main trial, this should minimise loss of diary information on which the primary outcome is based.

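### As worded, the multiple imputation of missing costs and EQ-5D names only baseline covariates, not the follow-up values and diary falls that the trial already collects

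*Protocol article*

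**What the plan says.** The only statement on missing economic data is in the protocol article, Economic analysis: "Missing cost and QOL data will be explored by employing multiple imputation methods [45,46] using alternative configurations of baseline covariates". It names one class of predictor and says that the choice within that class will be varied. The same section promises analyses "adhering to good practice for economic evaluations alongside clinical trials [43,44", without giving an imputation model.

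Other sections show what else is available for a participant with a missing visit:
- Abstract, Methods/Design: "Data will be collected at baseline, three, six and twelve months". Table 1 lists both EQ-5D and resource use at all four times.
- Follow-up assessment: "Participant quality of life (QOL) data will be collected using the EuroQOL EQ-5D instrument [37] during assessment visits", so a participant who misses one visit may well have values from the others.
- Follow-up assessment: "Fall data will be collected using monthly, prospective, self-report diaries for twelve months following randomisation", and "Additional resource use will be collected within the fall dairies".

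For the other secondary outcomes, the Statistical analysis section plans "mixed normal models for repeated measurements at 3, 6 and 12 months controlling for centre, Hoehn and Yahr score, and baseline value". People with only part of their follow-up stay in those models.

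**The concern.** Someone who misses the 12-month visit will often have 3- and 6-month EQ-5D, costs and diary falls. Imputing the missing value from baseline alone treats two people with the same baseline as interchangeable, even if one has deteriorated and is falling repeatedly. That is valid only if, given baseline, missingness is unrelated to interim health. Swapping one set of baseline covariates for another makes the same assumption each time, so the planned exploration could not expose a failure of it. The repeated-measures models for the other secondary outcomes use the interim values and so need a weaker assumption about the same people and visits.

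The difference between arms is harmed mainly when the link between interim health and missingness differs by arm. That is plausible here: participants know their allocation, and the intervention arm is offered up to twelve therapist sessions against a single physiotherapist visit for controls during follow-up. At stake are the incremental QALYs, by the same logic the incremental costs, and hence the ICER. Cost-effectiveness is a stated aim of the trial.

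**Working it through.** The sentence at issue carries no figure to reproduce, so the question is how much a baseline-only model could matter.

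**Inputs from the documents.** Visits at 0, 3, 6 and 12 months; 1:1 allocation; 600 recruits less 10% before randomisation = 600 × 0.90 = 540, or 270 per arm. The only post-randomisation loss figure is 5% at 6 months. There is none for 12 months or for missing EQ-5D or costs, and no EQ-5D SD, correlation or expected gain. All of these are assumed below.

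**QALY formula (area under the curve, in years).**
0.25(E0+E3)/2 + 0.25(E3+E6)/2 + 0.5(E6+E12)/2 = 0.125·E0 + 0.25·E3 + 0.375·E6 + 0.25·E12.
If only E12 is imputed, an error δ in its arm difference moves the incremental QALY by 0.25δ.

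**Simulation A.** 270 per arm; SD 0.25; correlation of E12 with E0, E3 and E6 of 0.5, 0.6 and 0.7. Alone, E6 therefore explains 0.7² = 49% of the variance of E12, against 0.5² = 25% for E0. Gain 0.04 at each follow-up visit, so the true QALY gain is (0.25 + 0.375 + 0.25) × 0.04 = 0.035. E12 is missing with log-odds −2 and slope 1 per SD of E6. Imputation within arm, 5 imputations, 600 replicates.

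| Dependence of missingness on E6 | Missing, control / intervention | δ | 0.25δ | Bias, baseline-only | % of 0.035 |
|---|---|---|---|---|---|
| Same in both arms | 15.6% / 13.8% | −0.0012 | −0.0003 | −0.0003 | −0.9% |
| Intervention arm only | 11.8% / 13.9% | +0.0136 | +0.0034 | +0.0034 | +9.7% |
| Opposite directions in the two arms | 15.6% / 13.8% | +0.0278 | +0.0070 | +0.0070 | +20% |

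Adding E3 and E6 to the imputation model gives a bias of 0.0000 in all three rows.

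**Simulation B.** 540 randomised; SD 0.23; visit correlations 0.58 to 0.74; true gain 0.036. E12 is missing more often when E6 is poor, more strongly so in controls. Estimate adjusted for baseline EQ-5D; 10 imputations, 500 trials per scenario.

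| Missing at 12 months | 12% | 22% | 31% |
|---|---|---|---|
| E12 imputed from baseline + arm | 0.0338 | 0.0328 | 0.0320 |
| Shortfall against 0.036 | 6.1% | 8.9% | 11.1% |
| E12 imputed with E3 and E6 added | 0.0359 | 0.0362 | 0.0362 |

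The run itself reported 7 to 12%. The difference is within the rounding of the true gain: 0.0365 would give 1 − 0.0338/0.0365 = 7.4% and 1 − 0.0320/0.0365 = 12.3%. When the dependence is equal in both arms and arm is in the model, the bias is 5% or less.

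**Reading the two together.** The signs differ because the arm with the stronger dependence differs: the intervention arm in A, controls in B. The direction in the real trial cannot be predicted. The 20% end needs missingness to run in opposite directions in the two arms, which is an extreme case. Neither simulation includes costs or diary falls.

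**The case against.** The strongest reply is that the sentence excludes nothing. When costs and EQ-5D at several visits are imputed together by chained equations, the incomplete variables normally predict one another. The baseline covariates are then the extra predictors that the analyst chooses, and varying that choice fits this reading. The article is condensed, the full imputation model may sit in another document, and the wording suggests an exploratory role rather than the base case. The general commitment to good practice may lead the analysts to the fuller model anyway.

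Much of this stands, and it rules out four stronger readings that a reader might infer:
- That the plan discards the 3- and 6-month values and diary falls. It does not name them, which is not the same.
- That allocation is left out, pulling the arms together. Nothing says that arm is omitted or that the arms are pooled.
- That the bias could reach 25 to 50%. In simulation B, imputing the QALY total from baseline + arm gave 0.0271, 0.0219 and 0.0183, which is 25%, 39% and 49% below 0.036. That needs totals to be imputed, baseline-only predictors and arm-differential drop-out all at once, and the article does not say that totals are imputed.
- That the economic and clinical analyses contradict each other. They use different methods for different quantities, and their missing-data assumptions diverge only if the imputation is baseline-only.

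The possible bias is also modest against sampling error. In simulation B it is 0.0022 to 0.0040 with a standard error of about 0.0115, or 0.19 to 0.35 standard errors.

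What does not stand is that this is merely detail left for later. The article specifies a predictor class and what will be varied. An analyst who follows it literally would leave out the best predictors in every variant.

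**Conclusion.** The point holds as a weakness of wording with a conditional consequence: a cheap improvement of minor severity. A model truly limited to baseline covariates would rest on an untested assumption and could shift the incremental QALYs. Under assumed inputs the shift is near zero to 5% with equal drop-out dependence in both arms and arm in the model. With arm-differential dependence and visit-level imputation it is roughly 7 to 20%, of unpredictable sign. Including the interim values essentially removes it.

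These sizes rest on assumed SDs, correlations, gains and 12-month missingness of about 12 to 31%. In simulation B the bias fell as missingness fell, so it would be smaller if missingness stayed near the 5% that the article expects to lose by 6 months. The effect on costs is a matter of reasoning only. The primary falls analysis does not use this imputation.

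**What to change.** Replace the sentence with wording such as:

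*Missing EQ-5D and cost components will be multiply imputed at visit level, separately by arm, from baseline covariates together with all observed 3-, 6- and 12-month EQ-5D and cost components and diary fall counts. QALYs and total costs will be derived after imputation. Imputation from alternative sets of baseline covariates will be reported as a sensitivity analysis.*

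If joint imputation across visits was intended all along, this simply says so. The cost is one sentence and a somewhat larger imputation model. No new data are needed, and the baseline-covariate configurations already planned are kept.

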### Nested qualitative study

A longitudinal qualitative study will be conducted alongside the main trial to explore the impact of Parkinson’s on daily life and the expectations and experiences of participants allocated to the intervention study arm. The study will draw on the principles of grounded theory [48,49] and use a maximum variation sampling strategy [50] addressing age (≤ 80 years; > 80 years), gender, falls in previous year (1 fall; 2–10 falls; > 10 falls), disease severity (each of Hoehn and Yahr stages 1–4) and centre (Southampton, Portsmouth, Bournemouth, Exeter). Semi-structured interviews [51] using a topic guide will be conducted with forty participants (ten from each study site) or as many as needed to ensure data saturation, from the intervention arm of the study, in their own home. Each participant will be interviewed twice, firstly after screening but before the intervention commences, and secondly, six months after completion of the intervention. All interviews will be digitally recorded, transcribed verbatim and supplemented by a researcher diary [52]. Analysis will comprise initial, focused, axial and theoretical coding in order to develop interpretive theories conceptualising the experience of participating in PDSAFE. The qualitative researcher will keep a research diary throughout, and will compare coding of initial interviews with a second researcher to promote sensitivity and reflexivity [52]. Supervisory meetings will ensure that preliminary interpretation is open to scrutiny, and that each iteration is shared and tracked. These strategies will help to ensure that rigour is maintained in the conduct and analysis of this sub-study. Along with self-reported dairies of home exercises, the longitudinal qualitative study will contribute more detailed information about factors influencing adherence.

## Discussion

The physical, psychological and economic consequences of falls among PwP are costly in both human and financial terms. This aims of this trial are to establish the effectiveness and cost-effectiveness of a novel, home-delivered physiotherapy intervention (PDSAFE) compared with usual care on risk of falling for people with Parkinson’s who have a history of falling.

PDSAFE is a novel intervention that builds upon the existing literature and targeting known risk factors, being the first trial that uses a novel delivery modus (technology) in conjunction with traditional physiotherapeutic approaches. This will be the largest trial of aiming to reduce falls for PwP to date. The inclusion of a nested qualitative study will aid understanding of the processes and mechanisms of the intervention and outcomes.

If effective, this intervention has the potential to improve the physiotherapy care and therefore patient and service level outcomes for PwP.

## Abbreviations

CES: *Carer Experience Scale*
CRN: *Clinical Research Network*
CSI: *Caregiver Strain Index*
EQ-5D: *EuroQOL -5D*
MMSE: *Mini Mental State Examination*
MoCA: *Montreal Cognitive Assessment*
NIHR: *National Institute of Health Research*
PwP: *People with Parkinson’s*
QALY: *Quality adjusted life years*
QOL: *Quality of life*
